**Methods:**

This will be a multicenter three-armed randomized, double-blind, placebo-controlled, prophylactic intervention study in critically ill patients. We will include consecutive non-neurological ICU patients, aged ≥18 years with an expected ICU length of stay >1 day. To be able to demonstrate a 15% increase in 28-day survival time with a power of 80% and alpha of 0.05 in both intervention groups, a total of 2,145 patients will be randomized; 715 in each group. The anticipated mortality rate in the placebo group is 12%. The intervention groups will receive prophylactic treatment with intravenous haloperidol 1 mg/q8h or 2 mg/q8h, and patients in the control group will receive placebo (sodium chloride 0.9%), both for a maximum period of 28-days. In patients who develop delirium, study medication will be stopped and patients will subsequently receive open label treatment with a higher (therapeutic) dose of haloperidol. We will use descriptive summary statistics as well as Cox proportional hazard regression analyses, adjusted for covariates.

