### Objectives

Definitions of variables in objectives are reported in Table 1.

**Table 1 T1:** Definition of study objectives

**Objective**	**Definition**
*Survival days in 28 days*	Number of days that patients survive in 28 days. All patients will be classified as either ‘alive at study day 28’ or, if dead, ‘dead at study day 28’ on an intention-to-treat basis.
*Delirium diagnosis*	Patients are diagnosed as delirious when they have at least one positive CAM-ICU screening during their complete ICU stay. Patients who were not delirious during their ICU-stay are considered as non-delirious patients.
*Delirium-and-coma-free days in 28 days*	Number of days that the patient is alive and not delirious and not in coma over 28 days starting from the day of inclusion. A delirium-and-coma-free day is defined as a negative CAM-ICU screening with a Richmond Agitation Sedation Score (RASS) greater than (more alert than) -3/-4/-5 during a day. In case a delirious patient is discharged to the ward, a delirium-free day is defined as a delirium observation scale score [30] of less than 3 during a complete day.
*Duration of mechanical ventilation*	Time in days that the patient is on the mechanical ventilator. If the patient is ventilated mechanically several times during one ICU admission, then the ventilator times are added. Both invasive and non-invasive ventilation will be registered. Ventilator-free days (in 28 days) will be calculated.
*Incidence of re-intubation*	Patients who need to be intubated within 28 days from randomization, following a previous extubation, irrespective of the reason for re-intubation, are counted as incident case for re-intubation.
*Incidence of ICU readmission*	Patients who need to be readmitted to the ICU during within 28 days from randomization, irrespective of the reason for readmission, are counted as incident cases for ICU readmission.
*Side effects*	Drowsiness, agitation, QTc-time prolongation (using 12-leads ECG or monitor strip with Bazett’s formula) and development of extra pyramidal symptoms such as tandem gait, dystonia, tremor, myoclonus, tics, rigidity, akathisia [31], determined daily by physical examination by the intensivist.
*Serious adverse event*	Any untoward medical occurrence or effect at any dose that results in one of the following outcomes and is not classified as a clinical outcome of delirium or the underlying disease using the description above:

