	- death that is not related to the underlying disease or sequel of the underlying disease, or death that is considered by the investigator to be related to study drug
	- prolonged inpatient hospitalization or re-hospitalization
	- a life-threatening experience (that is, immediate risk of dying)
	- persistent or significant disability/incapacity
	- congenital anomaly/birth defect
	- considered significant by the investigator for any other reason
*Sudden unexpected serious adverse reactions*	Unexpected adverse reactions are adverse reactions, of which the nature, or severity, is not consistent with the applicable product information. Adverse reactions are all untoward and unintended responses to an investigational product related to any dose administered.

#### **
*Primary objective*
**

To determine the effect of prophylactic haloperidol use on 28-days survival.

#### **
*Secondary objectives*
**

There are seven secondary objectives:

1. To determine the effect of prophylactic haloperidol use on 90-day survival; survival analysis stratifying for delirium incidence will be performed.

2. To determine the effect of prophylactic haloperidol use on the incidence of delirium.

3. To determine the effect of prophylactic haloperidol use on the number of delirium- and coma-free days in a period of 28 days.

4. To determine the effect of prophylactic haloperidol use on delirium related outcomes: time to successful extubation, incidence of re-intubation, incidence of ICU readmission, and incidence of unplanned removal of tubes and catheters.

5. To evaluate the incidence and severity of side effects of haloperidol prophylaxis.

6. To determine the effect of preventive haloperidol use on quality of life 1 and 6 months following ICU admission compared with a baseline measurement at ICU admission using the Short Form-12 (SF-12) questionnaire.

7. *A priori* defined post-hoc analyses:

a. To determine the preventive effectiveness of haloperidol in different patient groups based on the *a priori* risk to develop delirium: patients with a predicted risk up to 50%, 50–70%, 70–90%, above 90% will be evaluated.

a. To determine the preventive effectiveness of haloperidol in different patient groups: medical/surgical/trauma patients, per acute physiology and chronic health evaluation-II (APACHE-II) score (<20, 20–25, >25)

a. Effectiveness of prophylaxis when delirium is diagnosed based on 1, 2, or more days with positive CAM-ICU scoring.

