### Data collection

All data will be collected electronically in an electronic CRF (E-CRF). The E-CRF is a secured website where the participating hospitals must login using a unique password. Participating hospitals will only have access to their own data.

Demographic variables will be collected from all patients, including age, gender, PRE-DELIRIC score, APACHE-II score, and diagnosis group. Furthermore, outcome related variables will be collected (Table 2) as well as variables that may influence the delirium outcome, i.e., dexmedetomidine [32] and early mobilization [33]. Concerning the study medication, we will collect data on the amount of study drug administered as well as open-label haloperidol and other anti-delirium drugs administered in case delirium occurs.

**Table 2 T2:** Primary, secondary endpoints and posthoc analyses

**Primary endpoint**	**Secondary endpoints**	**Post-hoc analyses**
28-day mortality	90-day mortality Delirium incidence	Effectiveness in groups of predicted risk up to 50%, 50–70%, 70–90%, above 90% will be evaluated
	Number of delirium and coma free-days in 28 days	Effectiveness in diagnosis groups: medical, surgical and trauma patients
	Duration of mechanical ventilation	Effectiveness per APACHE-II score: <20, 20–25, >25
	Incidence of unintended tube or catheter removal	Effectiveness in groups with 1, 2, or more positive CAM-ICU scores
	Incidence of ICU re-admission	
	Quality of life measured at time of ICU admission, after 1 and 6 months using SF-12	
	Incidence and severity of side effects of prophylactic haloperidol (all patients)	

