**Figure 1 F1:**
[figure not shown]
CONSORT flowchart of patient enrollment.

A safety, futility, and superiority interim analysis will be performed by the DSMB after 175, 350, 500 (safety and futility) and 1,000 (safety and superiority) patients are included. Differences in serious adverse events between intervention and placebo are used for safety analyses and the primary endpoint 28-day survival is used to determine futility or superiority of intervention or placebo.

After the inclusion of 1,000 patients, superiority will be tested. A proven superiority (*P < 0.003, two-sided)* of any dose of haloperidol over placebo or a proven superiority (*P < 0.003, two-sided)* of placebo over haloperidol determined during the interim analysis will result in an alpha of 0.049 (two-sided) for the final analysis. This alpha distribution was calculated by an independent statistician according to the method of Lan-DeMets cumulative alpha spending function of O’Brien-Fleming alpha spending [36].

Data will be analyzed according to the intention-to-treat principle. For the descriptive statistics, continuous variables will be given as mean with standard deviation or median and inter quartile ranges, depending on their distribution. Normally distributed variables will be tested using Student’s *t*-test for comparison and Mann-Whitney U-tests for non-normally distributed variables. Categorical (and binary) variables will be presented as numbers and percentages and will be analyzed using the χ^2^ test. Survival analyses with Kaplan-Meier curves will be used as graphical representation. Cox proportional hazard regression analyses will be used to estimate the hazard ratio for survival with the use of haloperidol versus placebo. Furthermore, we will perform adjusted analyses for relevant covariates (including delirium, APACHE-II score, age, sex, sepsis, and other differences between the three study groups irrespective of the possible imbalance between the three groups). For this covariate analysis, univariate logistic regression analysis will be performed first in order to test the strength of the relationship. Subsequently, variables significantly associated with the dependent variable will be included in the covariate analyses.

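### The objectives and Table 2 name different ventilation outcomes, and the one in Table 2, raw duration, has no rule for death; the planned ventilator-free days are in neither list.

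*Protocol article*

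**What the plan says.** The protocol article describes the ventilation outcome in three places.

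- **Secondary objectives, item 4.** The delirium-related outcomes are "time to successful extubation, incidence of re-intubation, incidence of ICU readmission", followed by unplanned removal of tubes and catheters.
- **Data collection, Table 2 (endpoints).** The ventilation entry is "Duration of mechanical ventilation". Time to successful extubation and re-intubation are absent; ICU readmission and tube removal are present.
- **Objectives, Table 1 (definitions).** Duration is "Time in days that the patient is on the mechanical ventilator". Repeat episodes within one ICU admission are added, and invasive and non-invasive ventilation are both registered. The same entry then says "Ventilator-free days (in 28 days) will be calculated". Re-intubation is defined; time to successful extubation is not.

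For analysis, the section Sample size calculation and statistics gives Student's t-test for normally distributed variables and "Mann-Whitney U-tests for non-normally distributed variables". Cox regression is described for survival only: "Cox proportional hazard regression analyses will be used to estimate the hazard ratio for survival".

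The abstract says "The anticipated mortality rate in the placebo group is 12" per cent, and the primary endpoint is 28-day survival.

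**The concern.** There are two linked problems.

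First, the list of objectives and the list of endpoints disagree on what will be measured. The candidate measures are not interchangeable. Summed duration includes non-invasive support and repeat episodes. Time to extubation applies only to intubated patients and needs a definition of success. Ventilator-free days run over a fixed 28-day window. With none of them designated, the measure reported could be chosen after the results are known.

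Second, the measure in Table 2 responds to death in the wrong direction. A patient who dies early on the ventilator contributes a short duration, which a t-test or rank test reads as a good result. The trial is designed to detect a difference in survival, so the arms are expected to differ in the event that cuts ventilation short.

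**Working it through.** **1. The text set side by side**

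| Measure | Objective 4 | Table 1 | Table 2 |
|---|---|---|---|
| Time to successful extubation | named | not defined | absent |
| Duration of mechanical ventilation | absent | defined, no death rule | named |
| Ventilator-free days in 28 days | absent | mentioned under duration, no death rule | absent |
| Re-intubation | named | defined | absent |

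No ventilation measure appears in both the objectives and Table 2. For contrast, Table 1 does deal with death in the parallel delirium outcome: "Number of days that the patient is alive and not delirious and not in coma over 28 days".

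**2. Direction and size of the effect of death on raw duration**

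The plan gives no figure to reproduce here, so this is an illustration.

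Inputs from the article:
- 28-day placebo mortality of 12% (abstract).
- A hazard ratio of 0.85 (Sample size calculation and statistics), taken as a benefit of haloperidol. Applied as a simple ratio, 0.12 × 0.85 = 10.2%. Under proportional hazards, 1 − 0.88^0.85 = 10.3%.

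Assumptions not in the article:
- Every patient is ventilated from day 0.
- Extubation is exponential with a mean of 6 days and is identical in all arms.
- Death is exponential and independent of extubation.
- Ventilator-free days are zero if the patient dies by day 28.

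Formulas, for 28-day mortality m:
- Death hazard: d = −ln(1 − m)/28. Total hazard: h = 1/6 + d.
- Mean ventilator days to day 28: (1 − exp(−28h))/h.
- Mean ventilator-free days: (1 − m) × [28 − 6(1 − exp(−28/6))] = (1 − m) × 22.06.

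| 28-day mortality | h | Mean ventilator days | Mean ventilator-free days |
|---|---|---|---|
| 12% | 0.17123 | 5.79 | 19.4 |
| 10.2% | 0.17051 | 5.82 | 19.8 |
| 18% | 0.17375 | 5.71 | 18.1 |
| 15% | 0.17247 | 5.75 | 18.7 |
| 30% | 0.17941 | 5.54 | 15.4 |

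- About the planned effect (12% against 10.2%): 5.815 − 5.792 = 0.02 day more ventilation in the arm with fewer deaths. A simulation of one million patients per arm under the same assumptions gave 5.80 against 5.83, or 0.03 day; the gap from the formula is simulation error. Using 10.3% also gives 0.02 day (5.814 − 5.792).
- 12% against 18%: 5.79 − 5.71 = 0.08 day in favour of the arm with more deaths.
- 15% against 30%: 5.75 − 5.54 = 0.21 day in the same direction.

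Extubation is identical in every row, so the differences in duration come from death alone. Ventilator-free days, with death as zero, move the other way: 19.8 − 19.4 = 0.4 day better in the arm with fewer deaths.

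**3. Set against sampling error**

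With 715 patients per arm and an assumed standard deviation of 6 days, the standard error of a difference in means is 6 × √(2/715) = 0.32 day. A shift of 0.02 to 0.03 day is at most about a tenth of that.

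**The case against.** The strongest reply is that this is a labelling mismatch in one component of one of seven secondary objectives, with no alpha or power attached. Three parts of it deserve weight.

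- **Ventilator-free days may be the intended form of the endpoint.** They stand inside the Table 1 definition of the outcome that Table 2 lists, so they may be how duration was to be analysed. That reading is plausible, but the text does not say so, and it would still leave objective 4 naming something else.
- **Handling of death can be left to the analysis plan.** For time to extubation this stands. A reader might infer that this measure is distorted by death as well, but that depends on whether death is censored, excluded or treated as a competing event. The article does not say, and need not at this level of detail. A reader might equally infer that ventilator-free days, as written, already account for death. They do not: no scoring of deaths is given for them, and the requirement to be alive belongs to delirium-and-coma-free days.
- **The distortion is very small at the planned mortality.** This also stands. The calculation gives a few hundredths of a day. Larger shifts need either mortality contrasts that this trial does not anticipate or invented ventilation times for the patients saved.

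The mismatch itself is untouched by these replies. It is a disagreement between two lists in one article, not a detail deferred elsewhere.

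**Conclusion.** The point holds as an inconsistency with a modest analytic consequence. The objectives and Table 2 name different ventilation outcomes, time to successful extubation is undefined, re-intubation is missing from Table 2, and ventilator-free days are planned but listed in neither place.

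Raw duration, as defined and with the tests given, is biased in favour of an arm with more deaths. The direction follows from the definition. The size, about 0.02 to 0.03 day near the planned effect, rests on the assumed 6-day mean, exponential times and all patients being ventilated. It would not by itself alter the trial's conclusions. The better reason to act is that one prespecified measure removes the choice among several, and the improvement is nearly free.

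**What to change.** Name one ventilation endpoint, in the same words, in objective 4, Table 1 and Table 2. The preferred choice is ventilator-free days to day 28, since it is already to be calculated, with the rule that death by day 28 scores zero. Report raw duration descriptively, and add re-intubation to Table 2.

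If time to successful extubation is kept instead, define success in Table 1 and treat death as a competing event; that would also resolve the point.

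The cost is a few wording changes and no new data. The drawback of ventilator-free days is that they mix death with time on the ventilator. A difference could come from mortality alone, as in the illustration, so the components (deaths by day 28, and ventilator days in survivors) should be shown next to the composite.

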### Study population

#### **
*Inclusion criteria*
**

All consecutive critically ill patients admitted to the ICU aged ≥18 years at the time of ICU admission and with an expected length of ICU stay of over one day will be included as informed consent is obtained.

Data from patients that are included in the study, but who do not receive any study drug and are discharged from the ICU within 24 h will be discarded from further analysis. Patients who received at least one dose will remain in the study and patients in whom study medication had to be halved or stopped, e.g., because of prolonged QTc time or other side effects, will remain allocated to their study group and analyzed on an intention-to-treat basis.

#### **
*Exclusion criteria*
**

The following will be considered exclusion criteria: no informed consent obtained; history of epilepsy, Parkinson’s disease, hypokinetic rigid syndrome, dementia or alcohol withdrawal syndrome; patients admitted to the ICU for any other neurological disease (including post-cardio-pulmonary resuscitation patients, and patients admitted with coma due to overdose); patients treated with anti-psychotic therapy over the last 30 days prior to ICU admission; prolonged QTc-time (>500 msec) or history of clinically relevant ventricular arrhythmia in last 12 months; pregnancy/breast feeding; documented delirium prior to ICU admission; reasons that impair delirium assessment with the CAM-ICU (serious auditory or visual disorders, unable to understand Dutch or English; severely mentally disabled; serious receptive aphasia); ICU-stay less than one day; moribund and not expected to survive two days; known allergy to haloperidol.

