### Safety monitoring and safety issues

A Data Safety Monitor Board (DSMB) is established for this study to perform ongoing safety surveillance and to perform interim analyses on the safety data. This is an independent committee composed of two physicians/researchers (a psychiatrist and an anesthetist) and a statistician. The DSMB will perform all interim analyses. To assess side effects of haloperidol and to determine superiority of the intervention or placebo the DSMB will be unblinded for this study, while all researchers remain blinded. Furthermore, the study will be monitored by an independent researcher who will monitor the trial master file, and perform random checks of informed consent forms, drug accountability lists, and source data of primary and secondary outcome measures.

Concerning safety issues, during a patient’s treatment with the study medication, known side effects of haloperidol [34] are pro-actively collected with a special focus on prolonged QTc-time, drowsiness, extrapyramidal symptoms, and agitation and sedation effects. All side effects will be collected during patients’ treatment with the study medication until 24 h after stopping the study medication. In case of the occurrence of side effects, physicians can reduce the dosage or stop the study medication, depending on the severity of the occurred side effect and at the discretion of the attending physician. Only for prolonged QTc-time, strict stopping rules are applied, as described below. To detect side effects of haloperidol, the protocol dictates that patients are physically examined every day for known signs of extrapyramidal symptoms (signs of Parkinsonism and/or akathisia and/or dystonia). Furthermore, daily QTc-time is calculated using a 12-lead ECG or a monitor lead ECG. A QTc-time of over 500 msec combined with an increase of over 10% of baseline QTc-time is defined as prolonged QTc-time. In case of QTc-time prolongation, the study drug is temporarily stopped until QTc-time is normalized. After normalization of QTc-time (<500 msec) the study drug will be restarted. If QTc-time becomes prolonged again, the study drug will be stopped definitively. The patient will remain allocated to the original study group.

To determine long-term side effects, such as rigidity, and quality of life, a recommended and validated quality of life questionnaire, SF-12 [35], is taken at the time of admission and is sent to the patients 1 and 6 months after ICU admission.

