### Ethics

The study will be conducted according to the principles of the Declaration of Helsinki (version 2008) and in accordance with the Medical Research Involving Human Subjects Act.

There are indications that early treatment of delirium is more effective than delayed treatment [37], but this needs to be confirmed in other studies. Since it is recognized that the onset of delirium occurs, on average, on day 2 after ICU admission, early preventive treatment is likely to be more effective. In the short-term, low dose haloperidol has no known relevant side effects, therefore randomization and administration of study medication will be started immediately following identification of a high-risk patient. When an informed consent procedure results in a delay of randomization, a deferred consent procedure may be followed. The informed consent procedure will be started as soon as possible, but always within 24 h following ICU admission. If no deferred informed consent can be obtained within 24 h, the patient will be excluded from the study and study drug administration will be stopped.

The medical ethical committee of Arnhem-Nijmegen (CMO) approved this study including this deferred consent procedure (CMO-number 2012/424). This trial is registered on clinicaltrials.gov: NCT01785290.

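### SF-12 at 1 and 6 months is to be related to an admission baseline, but the stated two-sample tests do not adjust for that baseline, so precision is lost.

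*Protocol article*

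**What the plan says.** Under Objectives, secondary objective 6 is the effect of haloperidol on quality of life 1 and 6 months after ICU admission, "compared with a baseline measurement at ICU admission using the Short Form-12 (SF-12) questionnaire". Table 2 under Data collection lists the endpoint as "Quality of life measured at time of ICU admission, after 1 and 6 months using SF-12". Safety monitoring and safety issues adds that the questionnaire "is taken at the time of admission and is sent to the patients 1 and 6 months after ICU admission".

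Sample size calculation and statistics gives one general rule for continuous variables: "Normally distributed variables will be tested using Student’s" t-test, and "Mann-Whitney U-tests for non-normally distributed variables". After the Cox regression sentence the same section says "we will perform adjusted analyses for relevant covariates (including delirium, APACHE-II score, age, sex, sepsis, and other differences between the three study groups". Those covariates are screened by univariate logistic regression and kept if significant. Baseline SF-12 is not named among them.

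Two other statements bear on whether a baseline will exist. The population is "All consecutive critically ill patients admitted to the ICU aged ≥18 years at the time of ICU admission" with an expected stay of more than one day. Ethics allows dosing before consent: "When an informed consent procedure results in a delay of randomization, a deferred consent procedure may be followed".

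**The concern.** The objective ties the follow-up scores to a baseline, but the stated tests either ignore that baseline or use it inefficiently. Two readings are open, and they cost different things.

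- **Follow-up scores alone are tested.** No patient is lost for want of a baseline, but the collected baseline goes unused and the objective is not analysed as worded.
- **Changes from baseline are tested.** The baseline is used, but less efficiently than as a covariate, and patients without an admission SF-12 leave the comparison.

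At stake is the precision of a secondary outcome. On the second reading, it is also how well the analysed patients represent those randomised. Some missing baselines are foreseeable in consecutive critically ill admissions. In a patient dosed under deferred consent, an SF-12 completed only after consent would follow the first dose and would not be a true baseline.

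**Working it through.** **Inputs.** The article gives no SD, effect size, correlation or completion rate for SF-12, so there is no quality-of-life figure to reproduce. Its 647 and 715 patients per group were derived for survival and say nothing about SF-12. The correlation r between baseline and follow-up is therefore assumed, with range 0.3 to 0.7. Baseline and follow-up are taken to have equal SD. The formulas describe the t-test; the Mann-Whitney test does not adjust for baseline either.

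**Step 1: relative variance of the arm difference in the same patients**, in units of the follow-up variance:

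- follow-up scores alone: 1
- change from baseline: 2(1 − r)
- ANCOVA: 1 − r²

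Dividing by the ANCOVA variance gives 1/(1 − r²) for follow-up alone and 2(1 − r)/(1 − r²) = 2/(1 + r) for change.

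| r (assumed) | Follow-up alone | Change | ANCOVA | Follow-up alone ÷ ANCOVA | Change ÷ ANCOVA |
|---|---|---|---|---|---|
| 0.3 | 1 | 1.40 | 0.91 | 1.10 | 1.54 |
| 0.5 | 1 | 1.00 | 0.75 | 1.33 | 1.33 |
| 0.7 | 1 | 0.60 | 0.51 | 1.96 | 1.18 |

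ANCOVA has the smaller variance on both readings for every r strictly between 0 and 1. The two alternatives are equal at r = 0.5. Change is the worse of the two below that value and the better above it.

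**Step 2: patients lost if change is tested.** As an illustration, take the 12% placebo mortality in the abstract for every arm and assume full response: 715 × 0.88 = 629 assessable per arm. If the admission SF-12 exists for 70%, 50% or 30% of them (assumed), a change-score analysis keeps 440, 315 or 189.

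**Step 3: both losses together, one example.** Take r = 0.5 and 50% of baselines available, with missingness unrelated to arm. The SE of the arm difference, in SD units, is:

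- change, complete cases: √(2/315 × 1.00) = 0.080
- follow-up alone, all responders: √(2/629) = 0.056
- ANCOVA keeping all responders with a missing-baseline indicator: √(2/629 × (1 − 0.5 × 0.25)) = 0.053

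The 629 is itself uncertain. The 18-day median survival used for the sample size would, under exponential survival, leave 0.5^(28/18) = 34% alive at day 28, about 243 per arm. The ratios in Step 1 do not depend on this number.

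**The case against.** The strongest reply is that the article never specifies a t-test of change. Objective 6 speaks only of a comparison with baseline. The t-test and Mann-Whitney sentence is a general line that follows the descriptive statistics. The covariate list is open-ended and could admit baseline SF-12. The exact SF-12 model, and any proxy or later completion of the admission questionnaire, are details that an article can leave to the full protocol or analysis plan.

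Much of this stands. The change score is an inference, which is why both readings are worked through. The covariate list does not rescue the plan, however. It follows the Cox model, is screened by logistic regression, which does not suit a continuous score, and would admit baseline SF-12 only through a data-driven step. The one test that the article does state for a continuous outcome is unadjusted.

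A reader might also infer four stronger things that the document does not support:

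- **Many patients cannot answer at admission.** No completion rate is given, and no respondent is named for the admission questionnaire. Deferred consent is tied to delay of randomisation, not to incapacity. Coma and ventilation days are outcomes over the stay, not status at entry. Several groups least able to answer are excluded.
- **The variance is at least doubled.** That requires an assumed share of missing baselines on top of an assumed correlation.
- **A change score is noisier than the follow-up score itself.** This holds only for r below 0.5.
- **The arm comparison is biased.** Baselines missing because of the patient's state at admission should be balanced between randomised arms in expectation. The harm is to precision and representativeness.

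**Conclusion.** The point holds in a limited form. The article collects a baseline SF-12 and builds objective 6 on it, yet the tests it states do not adjust for it. With r assumed between 0.3 and 0.7, the variance relative to ANCOVA is 1.10 to 1.96 times if follow-up scores are tested and 1.54 to 1.18 times if changes are tested. Only the second reading also loses patients without an admission SF-12, and the document does not allow that loss to be sized. This is one secondary outcome; the primary survival result is unaffected.

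**What to change.** State in objective 6 and in the statistics section that SF-12 scores at 1 and 6 months are compared between arms in all responders by linear regression (ANCOVA). Use SF-12 obtained before the first dose as covariate, with a missing-baseline indicator or simple imputation of the baseline. This replaces the unadjusted two-sample test for this outcome. Treat an SF-12 completed after the first dose as a missing baseline, because treatment could already have influenced it.

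The cost is a change of wording. No new questionnaire is needed, provided that the time of the admission SF-12 relative to the first dose is on record. The change does not deal with patients who die or do not return the questionnaire, and the report should say so.
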